#### Recruitment

At each participating site, enrolment will occur at outpatient clinics. With at least 25 sites, it is estimated that the trial will complete within 24 months of commencement. The trial opened for recruitment in April 2022 and the estimated completion date is April 2024.

#### Data collection methods

The electronic case report form (eCRF) system Marvin by XClinical will be used to collect data.

#### Patient-reported outcome measures

The International Index of Erectile Function and the International Prostate Symptom Score will be used to assess baseline erectile function and lower urinary tract symptoms, respectively. These questionnaires will aid the MDT decision making for treatment eligibility.

#### Patient retention

It is estimated that loss to follow-up will be no more than 20% due to the expected short time interval between enrolment and end of study. It is expected that the majority of patients will complete the trial within 4–6 weeks (tables 2 and 3).

**Table 2 T2:** Participant timeline in the trial: the timeline for men enrolled to the trial prior to undergoing MRI

	Contact with patient				
	Visit 0*	Visit 1	Visit 2	Visit 3	Visit 4
Screening	X	X			
PIS given	X	X			
Consent	X	X			
IIEF-5 and IPSS questionnaires	X	X			
mpMRI			X		
Radiologists report bpMRI (T2W and DWI only)			X		
Radiologists report mpMRI (T2W, DWI and DCE)			X		
MRI-targeted biopsy and systematic biopsy				X	
Test results given and treatment decision					X
Follow-up for further investigations from treatment decision					X
Serious adverse event	Complete as required at any time following registration				
Withdrawal form	Complete as required at any time following registration				

*Visit 0 is an optional teleconsult, depending on local practice. Note that, where applicable, more than one visit can take place on the same day, depending on local practice (eg, in centres where an MRI is performed on the same day as subsequent biopsies).

bpMRI, biparametric MRI; DCE, dynamic contrast-enhanced sequence; DWI, diffusion-weighted sequence; IIEF-5, International Index of Erectile Function; IPSS, International Prostate Symptom Score; mpMRI, multiparametric MRI; PIS, patient information sheet; T2W, T2-weighted sequence.

**Table 3 T3:** Participant timeline in the trial: the timeline for men enrolled after undergoing mpMRI as part of routine care

	Contact with patient				
	Visit 0	Visit 1	Visit 2	Visit 3	Visit 4
Screening		X			
PIS given		X			
Consent		X			
IIEF-5 and IPSS questionnaires	X				
mpMRI		X			
Radiologists report bpMRI (T2W and DWI only)		X			
Radiologists report mpMRI (T2W, DWI and DCE)		X			
MRI-targeted biopsy and systematic biopsy			X		
Test results given and treatment decision					X
Follow-up for further investigations from treatment decision					X
Serious adverse event	Complete as required at any time following registration				
Withdrawal form	Complete as required at any time following registration				

bpMRI, biparametric MRI; DCE, dynamic contrast-enhanced sequence; DWI, diffusion-weighted sequence; IIEF-5, International Index of Erectile Function; IP*SS*, International Prostate Symptom Score; mpMRI, multiparametric MRI; PIS, patient information sheet; T2W, T2-weighted sequence.

#### Statistical methods

A statistical analysis plan will be finalised before our database lock and before any statistical analysis occurs. A consort diagram will be presented. All continuous variables will be described using the mean and SD, or median and IQR, as appropriate. Categorical variables will be described using frequencies and percentages. Baseline characteristics will be examined and presented for those with and those without clinically significant PCa. The assumptions underpinning the statistical methods used will be assessed. The use of transformations will be considered to satisfy statistical assumptions.

#### Primary outcome analysis

The primary outcome is the difference in the proportion of men with clinically significant PCa, as detected by bpMRI-targeted biopsy compared with mpMRI-targeted biopsy. The proportion of men with clinically significant PCa, Gleason score of ≥3+4 or Gleason grade group of ≥2, detected by bpMRI-targeted biopsy, is defined as the number of men with clinically significant PCa identified on bpMRI-targeted biopsy divided by the number of men undergoing bpMRI. Similarly, the proportion of men with clinically significant PCa detected by mpMRI-targeted biopsy is defined as the number of men with clinically significant PCa identified on mpMRI-targeted biopsy divided by the number of men undergoing mpMRI. Methods that account for the paired nature of the data such as McNemar’s test will be used to compare bpMRI and mpMRI.

#### Secondary outcome analysis

The proportion of men with clinically insignificant cancer (any cancer core with Gleason score 3+3 or Gleason grade group 1) detected by bpMRI-targeted biopsy will be compared with that of mpMRI-targeted biopsy. The proportion of men with clinically insignificant cancer detected by bpMRI-targeted biopsy is defined as the number of men with clinically insignificant PCa identified on bpMRI-targeted biopsy divided by the number of men undergoing bpMRI. Similarly, the proportion of men with clinically insignificant cancer detected by mpMRI-targeted biopsy is defined as the number of men with clinically insignificant PCa identified on mpMRI-targeted biopsy divided by the number of men undergoing mpMRI. The same analytical approach described for clinically significant PCa will be applied.

The number and proportion of men scoring 1 or 2 (non-suspicious) or 3 (indeterminate) on bpMRI and mpMRI will be reported. A two-way table will be produced to show the agreement between the two MRI results using the Likert scoring system on a scale of 1–5.

The number and proportion of men with adequate standard of reporting on bpMRI and mpMRI will be reported.

A two-way table will be produced to show the number and proportion of patients with each radiological stage of bpMRI and mpMRI. Similarly, we will report the number and proportion of patients eligible for different treatment options following discussion of the bpMRI and mpMRI results in the MDT meeting.

Using histopathology as the reference standard, sensitivity, specificity, positive predictive value and negative predictive value with 95% CI of bpMRI and mpMRI will be reported. The following assumptions will be made, where non-suspicious MRI refers to a score of 1 or 2; suspicious MRI refers to a score of 3, 4 or 5 on the Likert and PI-RADS V.2.1 scoring systems; and absence of clinically significant cancer refers to a combination of clinical insignificant and no cancer.

The number and proportion of men with clinically significant cancer detected by systematic biopsy and not detected by bpMRI and mpMRI with targeted biopsy will be reported. A two-way table will be produced to show a comparison between systematic biopsy (no biopsy, clinically significant cancer, clinically insignificant cancer and no cancer) and the two MRI results with targeted biopsy (no biopsy, clinically significant cancer, clinically insignificant cancer and no cancer).

#### Sensitivity and other planned analyses

The primary outcome analysis will be repeated with a definition of clinically significant PCa being any primary pattern 4 disease with a Gleason score of 4+3 or a Gleason grade group of 3.

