### Objectives

The primary objective is to compare the detection of clinically significant PCa (Gleason score ≥3+4 or Gleason grade group ≥2) using bpMRI±targeted biopsy with mpMRI±targeted biopsy.

Key secondary objectives are:

To compare the proportion of men who have clinically insignificant PCa (Gleason score 3+3 or Gleason grade group 1) detected for bpMRI versus mpMRI.To compare the proportion of men with non-suspicious MRIs for bpMRI versus mpMRI.To compare the proportion of men with indeterminately scored MRI as reported by bpMRI and mpMRI.To compare the proportion of men with MRIs of adequate standard for reporting for bpMRI versus mpMRI.To compare the diagnostic test performance for bpMRI versus mpMRI.To compare radiological staging for bpMRI versus mpMRI.To compare treatment eligibility decisions for bpMRI when compared with mpMRI.To compare diagnostic performance of bpMRI and mpMRI when using the Likert scoring system in comparison to the Prostate Imaging Reporting and Data System (PI-RADS) V.2.1 scoring system.To compare the cost effectiveness of bpMRI when compared with mpMRI.

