### Outcomes

#### Primary outcome

The primary outcome will be the proportion of men with clinically significant PCa detected—any pattern 4 disease on any core (ie, Gleason score ≥3+4 or Gleason grade group ≥2). The time frame for assessment will be when biopsy results are available, at an expected average of 30 days post biopsy.

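### The sensitivity definition of clinically significant cancer is written as an exact grade instead of a threshold and contradicts its own opening words, so its handling of grade groups 4 and 5 is wrong or undefined

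*Protocol article*

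**What the plan says.** Under Sensitivity and other planned analyses, the article states: "The primary outcome analysis will be repeated with a definition of clinically significant PCa", the new definition being "any primary pattern 4 disease with a Gleason score of 4+3 or a Gleason grade group of 3". This is the only item in that section, and no other part of the article restates or extends the definition.

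The primary definition appears in several places, always as a threshold:

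- Objectives: "clinically significant PCa (Gleason score ≥3+4 or Gleason grade group ≥2"
- Primary outcome: "any pattern 4 disease on any core (ie, Gleason score ≥3+4 or Gleason grade group ≥2"
- Primary outcome analysis: "Gleason score of ≥3+4 or Gleason grade group of ≥2"

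The Abstract also carries ≥ on both terms. Clinically insignificant cancer, by contrast, is a single grade and is written as one: "any cancer core with Gleason score 3+3 or Gleason grade group 1" (Secondary outcome analysis).

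**The concern.** A stricter definition of clinically significant cancer should raise the lower cut-off and keep everything above it. This sentence raises the cut-off and, on its face, also sets an upper limit at the same grade. A man whose highest grade is 4+4 would be a case in the primary analysis and a non-case in the analysis meant to look at more serious disease.

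The proportions are taken over all men undergoing each MRI (Primary outcome analysis), so such a man stays in the denominator. If mpMRI-targeted biopsy alone finds his cancer, he is a discordant pair against bpMRI in the primary analysis. Under the literal sensitivity rule he becomes a concordant negative and carries no information. The repeat would then say nothing about whether bpMRI misses the highest grades.

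The wording also leaves the endpoint open to the programmer. One could follow the exact grade, another the opening words, and a third the presumed intention.

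**Working it through.** No figure in the article depends on this sentence, so the check is one of classification.

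**Inputs.** The primary rule and the sensitivity rule are as quoted above. The article itself pairs 3+3 with grade group 1, 3+4 with grade group 2 and 4+3 with grade group 3. For higher scores I assume the usual grouping: 4+4, 3+5 and 5+3 are grade group 4; 4+5, 5+4 and 5+5 are grade group 5.

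**Rules applied to each score.**

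| Highest grade | Primary (grade group ≥2) | Sensitivity, literal (exactly 4+3 or grade group 3) | Sensitivity, opening words alone (primary pattern 4) | ≥4+3 or grade group ≥3 |
|---|---|---|---|---|
| 3+3 (group 1) | no | no | no | no |
| 3+4 (group 2) | yes | no | no | no |
| 4+3 (group 3) | yes | yes | yes | yes |
| 4+4 (group 4) | yes | **no** | yes | yes |
| 4+5 (group 5) | yes | **no** | yes | yes |
| 5+3 (group 4), 5+4, 5+5 (group 5) | yes | **no** | **no** | yes |
| 3+5 (group 4) | yes | **no** | **no** | yes |

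**What the table shows.**

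1. The literal rule and the opening words agree only up to 4+3. They part at 4+4 and 4+5, so the sentence contradicts itself there.
2. Primary pattern 5 is a non-case on both readings. So is 3+5, which is grade group 4 with primary pattern 3.
3. Neither reading reproduces grade group 3 and above.

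**Is the missing ≥ a loss in text extraction?** Unlikely. The symbol survives in every statement of the primary definition, including the one in Primary outcome analysis shortly before.

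**Is an exact value just shorthand here?** The article's usage elsewhere does not suggest so. It writes ≥ for thresholds and a bare value for the one definition that is a single grade, clinically insignificant cancer.

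**The literal rule is also not monotone in grade.** Suppose each man is classified by his highest grade under each strategy (my assumption). A man with 4+3 in a target seen on both readings and 4+4 in an additional contrast-only target, which the MRI reporting rules allow, would count as detected by bpMRI and not by mpMRI. The reverse can happen when the higher grade lies in a bpMRI-only target. In both cases the strategy that found the higher grade is marked down.

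**Scale.** The Sample size section assumes 38% detection by mpMRI in 400 evaluable men, that is 0.38 × 400 = 152 men at grade group 2 or above. The men misclassified are the grade group 4 and 5 part of those, which the article does not give.

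**The case against.** The strongest reply is that everyone will know what was meant. The opening words already point to a stricter threshold, ≥ was probably omitted by oversight, and a trial statistician may well program grade group 3 and above. That is fair as to intent. It also rules out reading the sentence as a deliberate choice to exclude the highest grades: the sentence is self-contradictory, not a plain exclusion of 4+4. But guessing the intention does not repair the text. The qualifier narrows the opening words, and those words taken alone still leave out primary pattern 5.

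It could also be said that such details belong to the analysis plan, which is to be finalised before database lock. That would answer a missing definition. Here the article states one, and a plan that copied it would carry the error forward.

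A reader might go further and infer that the 5-point margin is carried over to this rarer endpoint, so that a non-inferior result is nearly automatic and a quarter to a half of the higher-grade cancers could be lost (5/20 = 25%, 5/10 = 50%). The documents do not support this:

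- The margin stands under Sample size. Primary outcome analysis, the analysis being repeated, names two proportions and a paired method and no margin. No non-inferiority verdict is announced for the sensitivity definition.
- The 10 to 20% prevalence behind those percentages is not in the article.
- The percentages treat the margin as a permitted observed loss, whereas the rule concerns the lower 95% bound. With 400 men, all discordance one way and a Wald interval, 13 men lost gives −0.0325 − 1.96 × √((0.0325 − 0.0325²)/400) = −0.0499, which passes. Fourteen gives −0.035 − 1.96 × √((0.035 − 0.035²)/400) = −0.0530, which fails. The largest observed loss that passes is thus about 3.25 points.

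Nor can a reader conclude that missed high-grade cancers would escape the trial's main result: the primary outcome counts them.

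**Conclusion.** The point holds as a defect in a stated definition. As written, the sensitivity endpoint is an exact grade that conflicts with its own opening words. Under the literal reading all grade group 4 and 5 men become non-cases in the only sensitivity analysis the article lists for the primary outcome. Primary pattern 5 is excluded under either reading.

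The reach is limited. The primary outcome and the sample size are unaffected, and the harm occurs only if the analysis is programmed from the sentence as it stands. The conclusion assumes the usual mapping of Gleason scores to grade groups 4 and 5, and that a stricter threshold was intended, which the context strongly suggests. Correction is worthwhile because the error lies in the definition itself and is easily carried into the analysis code.

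**What to change.** Under Sensitivity and other planned analyses, restate the definition as Gleason score ≥4+3 or Gleason grade group ≥3, if the investigators confirm that threshold. Remove the primary pattern 4 phrase, or reword it so that primary pattern 5 is included. Keep the grade group term, since it settles scores such as 3+5 without dispute. Carry the same wording into the statistical analysis plan before database lock.

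The cost is two symbols and one phrase. No data collection, sample size or primary analysis changes, because Gleason score and grade group are already reported overall and for each target.

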#### Monitoring

The National Cancer Imaging Translational Accelerator (NCITA) Global Prostate Trial Steering Committee (TSC) is responsible for the governance of the PRIME Study. A subgroup of independent TSC members form the data monitoring subcommittee (DMSC).

#### Roles and responsibilities of the TSC

The TSC’s role is to act as the oversight body for up to five PCa studies on behalf of the sponsor and funders. In addition, the independent members will form a DMSC to review safety. The role of the TSC is to provide oversight for the studies and advice through its chair to the chief investigators while working in tandem with the DMSC, sponsor, funders and host institution on all aspects of the studies. The rights, safety and well-being of the study participants are the most important consideration and should prevail over the interests of science and society.

#### Harms

Adverse events (AEs) will be defined as ‘any untoward medical occurrence in a clinical trial subject undergoing any intervention in the trial, which does not necessarily have a causal relationship with this treatment’.

Serious adverse events (SAEs) will be defined as ‘any untoward medical occurrence as a result of any intervention in the trial that:

Results in death,Is life-threateningRequires hospitalisation or prolongation of existing inpatients’ hospitalisation, results in persistent or significant disability or incapacity’.

AEs and SAEs will be recorded until 30 days post biopsy. In the event that the patient does not undergo biopsy, AEs and SAEs should be recorded until 30 days post MRI.

Unexpected AEs will be recorded by a member of the research team or clinical team on an AE report form or eCRF. All SAEs must be recorded on an SAE report form or eCRF, which must be sent to the coordinating trial unit within 24 hours of knowledge of the SAE. Both AEs and SAEs should be recorded in the medical notes.

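### The SAE definition carries a causal condition that the AE definition lacks, so a death or admission judged unrelated falls outside the 24-hour reporting rule

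*Protocol article*

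**What the plan says.** All the rules that matter are in the protocol article under Harms, apart from the participant timeline (Patient retention, Tables 2 and 3) and the oversight arrangements.

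- **AE definition.** An AE is an untoward occurrence in a participant undergoing a trial intervention, "which does not necessarily have a causal relationship with this treatment".
- **SAE definition.** An SAE is "any untoward medical occurrence as a result of any intervention in the trial that" results in death, is life-threatening, requires or prolongs hospitalisation, or leads to lasting or significant disability or incapacity.
- **SAE reporting.** "All SAEs must be recorded on an SAE report form or eCRF, which must be sent to the coordinating trial unit within 24 hours" of the SAE becoming known.
- **AE reporting.** "Unexpected AEs will be recorded by a member of the research team or clinical team on an AE report form or eCRF". No time limit is attached, and no duty to send the form to the trial unit.
- **Medical notes.** "Both AEs and SAEs should be recorded in the medical notes".
- **Window.** "AEs and SAEs will be recorded until 30 days post biopsy", or until 30 days after the MRI where no biopsy is done. No causal condition is attached.
- **Timeline.** The SAE row in Tables 2 and 3 reads "Complete as required at any time following registration".
- **Oversight.** Under the roles of the TSC, "the independent members will form a DMSC to review safety". Table 6 has the operations group report SAEs to the sponsor and ethics committee when necessary.

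**The concern.** One would expect an SAE to be an AE that is also serious, with relatedness assessed afterwards and recorded alongside. Here the two definitions treat cause differently. The AE definition sets it aside and the SAE definition requires it. Whether an event is serious enough to be expedited therefore depends first on a judgement that it was caused by a trial intervention.

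That matters because an early causality judgement can be wrong. An infection or a cardiac event in the weeks after a biopsy may be put down to a pre-existing condition. Expedited reporting regardless of cause exists so that someone outside the treating team can look at that judgement promptly. Under the printed wording, the events where the judgement is most open to question carry no duty of prompt central notification. With at least 25 sites in many countries, differing local thresholds for calling an event related would also alter the SAE count itself.

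**Working it through.** No sample size, rate or margin enters this point, and the plan states no figure to reproduce. The check is to apply the printed rules to one case and then look for text elsewhere that would change the result.

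**Step 1: the case.** A man is admitted to hospital 10 days after biopsy, and the admission is judged unrelated to the MRI or biopsy.

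| Question | Rule in Harms | Result |
|---|---|---|
| Inside the window? | Up to 30 days after biopsy, no causal condition | Yes |
| An AE? | No causal link needed | Yes |
| Meets a seriousness criterion? | Hospitalisation is listed | Yes |
| An SAE? | Must also result from a trial intervention | No |
| Sent to the trial unit within 24 hours? | SAEs only | Not required |
| Entered in the medical notes? | AEs and SAEs | Yes |
| Entered on a form or eCRF? | AEs that are unexpected | Only if unexpected |

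A death judged unrelated follows the same path.

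**Step 2: is the duty restored elsewhere?** The sections on monitoring, on the roles of the TSC, and on roles and responsibilities (Table 6) contain no second SAE definition and no separate expedited route for deaths or admissions judged unrelated. Table 6 deals with the onward reporting of events already classed as SAEs.

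**Step 3: does other text fit a causal condition?** Table 2 covers men enrolled before MRI. Screening and consent fall at Visit 0 or Visit 1, and the MRI is at Visit 2. The SAE row runs from registration, so it is open before any MRI or biopsy has taken place, when no event could result from either. The row and the window in Harms both read as if SAEs were captured by time rather than by cause. The argument from timing applies to Table 2 only, since the men in Table 3 have already had their scan when they enrol.

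**Step 4: direction and size.** If a share *u* of serious events in the window is judged unrelated, the number classed as SAEs is (1 − *u*) times the number of serious events. The count can fall but cannot rise. The documents give neither *u* nor an expected number of serious events, so no size can be derived.

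**The case against.** The strongest reply is that a broad AE class and a narrower class for expedited reporting can coexist. Nothing prevents both definitions from being applied, and limiting 24-hour reports to events caused by a trial intervention is a choice a sponsor may make. The wording reaches both MRI and biopsy, so harms recognised as procedural remain in scope. This stands in part. The definitions are inconsistent on causality, but they do not logically contradict each other, and that should not be claimed. The choice still gives the worse result, because a judgement that ought to be open to review decides whether the expedited report is made.

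A reader might go further and infer that such an event appears nowhere in the trial database, that the DMSC never sees it, or that a cluster of such events could not be detected. The documents support none of these:

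- Expectedness is not defined. If it is judged against the intervention, an admission from another cause could well count as unexpected and go on a form.
- The article does not say who judges causality. That the site does so is a reasonable inference, because the research or clinical team completes AE forms, but it is only an inference.
- The article does not say what the DMSC receives, and nothing limits it to SAE forms. Table 6 also gives the operations group data verification and central monitoring.

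Table 2 may show that the definition is loosely drafted and not used as a filter in practice. That is possible, but it is a reason to reconcile the passages.

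Finally, the article condenses a full protocol that is not shown, and SAE forms may already carry relatedness and expectedness fields. This limits what can be said about the forms. It does not remove the point, because the article prints the SAE wording as a definition in quotation marks. If the full protocol reads differently, the article misstates it; if not, the protocol needs the change.

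**Conclusion.** The point holds as a defect in a stated safety-reporting rule. On the printed wording, a serious event judged unrelated is not an SAE and is exempt from the 24-hour duty, and no other section brings it back. It remains an AE with a weaker and slower route: the medical notes in every case, and a form or eCRF if it is unexpected.

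The effect is one-directional, towards fewer SAEs, and its size cannot be stated from the documents. Any percentage for under-counting would rest on an assumed share of events judged unrelated, so none is offered. Harms are neither the primary outcome nor a listed secondary outcome, and every man has the full mpMRI. The comparison of bpMRI with mpMRI is therefore untouched, and what is at stake is safety oversight. The conclusion assumes that the definition is applied as printed.

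**What to change.** Remove the causal phrase from the SAE definition, so that an SAE is any AE that meets one of the listed seriousness criteria within the collection window. Record relatedness and expectedness as separate assessments of each SAE, if the form does not already do so. Onward reporting to the sponsor and ethics committee can stay restricted to related or unexpected events, so the wider definition need not widen those obligations. The definition, the window in Harms and the SAE row of Table 2 would then agree.

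The cost is one change of protocol wording, at most two fields on an existing form, and a modest number of extra SAE forms from about 500 men, most of whom are expected to complete the trial within 4–6 weeks. If the full protocol already carries a definition without the causal condition, correcting the article is enough.
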